### Study participants

A multi-point strategy will be applied to recruit a sufficient number of participants (in total 110 participants) with MD within a short timespan (approximately 1 month). Recruitment of participants will be performed by rehabilitation coordinators at county council rehabilitation centers, at primary care centers, rehabilitation centers and at private companies within the Stockholm area during early 2018. Participants will be given oral and written information about the trial at the rehabilitation centers and provide a written interest to participate. All participants will provide written informed consent before initializing the baseline assessments.

### Inclusion criteria

Currently, there are no agreed upon definitions of what constitutes a person with MD [26]. For the current study, participants are eligible if they are between 18 and 40 years of age with a MD, acquired within the past 3 years, and if they experience any mobility-related problems affecting their everyday life; for example, problems with dressing, performing household tasks, with transportation, personal hygiene tasks, or at work.

### Exclusion criteria

Exclusion criteria include being bound to a walker or wheelchair or having any medical condition not permitting moderate-intensity walking. Further exclusion criteria are not being able to speak/understand Swedish and not having access to a smartphone.

### Randomization

A block randomization procedure will be used at an individual level to ensure an equal distribution of participants between the two treatment groups. Participants will be randomized before the first baseline assessment at the healthcare center. The SAS Proc Plan (SAS Institute Inc., Cary, NC, USA) will be used for the randomization process. The block size will not be stated in the protocol so that the investigators are blind to the block size. Thus, limiting potential risk for selection bias.

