The intervention entails three face-to-face consultations, in groups of approximately 20 participants, held at the healthcare center. The first consultation, held at the start of the intervention (baseline), will focus on information on how to use the apps and improving motivation to increase walking and exercise, with additional discussions on goal setting and other techniques to support behavior change. The second PA consultation, held at week 6, will focus on semi-structured face-to-face interviews concentrating on facilitating and hindering factors associated with intervention adherence. Participants will review their progress towards achieving the goals set in the first meeting by discussing the information recorded on the walking app and the activity tracker. The final meeting at week 12 will focus on encouraging participants to maintain changes by reviewing goal attainment and discussing relapse prevention strategies to maintain healthy PA and other health habits. After 12 weeks, a purposive sample of participants are interviewed about their experiences of efficacy, implementation and outcomes of the app support and at 12 months with a focus on persistent changes of lifestyle.

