### Baseline assessment

Participants will be invited to group consultation meetings, including baseline assessments, at a healthcare center. The group consultations will be held at three time points and include all participants recruited from the different recruitment sources.

After a short introduction, participants will perform a battery of physical tests and fill in web-based questionnaires lasting, altogether, approximately 2 h. Thereafter, participants will be randomized into the two treatment groups, followed by separate introductions for their treatment. In addition to the questionnaires described below, the participants will fill in questions on basic demographic information. The baseline measures and all follow-up measures will be made in the morning (fasted state) in order to best utilize standardize measures (e.g. blood samples).

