### Primary outcome

The primary outcome, difference in time spent in MVPA per day at 12 weeks between the two groups, will be measured using the Actigraph GT3X+ tri-axial accelerometer (Actigraph, LCC, Pensacola, FL, USA), which has shown to accurately assess levels of PA under free-living conditions [27, 28]. Participants will be asked to wear the GT3X+ during all waking hours for seven consecutive days at baseline (week 0), midpoint (week 6), endpoint (week 12) and at maintenance follow-up (12 months). The minimum data requirement for inclusion in the analyses will be 10 h of data on at least 4 days, including one weekend day. Management and analyses of PA data will follow best practice and research recommendations [29]. In addition, we will analyze time spent in light and vigorous PA and sedentary time at all measure time points, as well as day-to-day data on steps/day from the participants’ smartphones (automatically stored in each smartphone “health kit” application).

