## Statistical analyses

### Primary and secondary outcome measures

The primary study outcome, difference in levels of MVPA at 12 weeks between the two treatment groups, will be tested on an intention-to-treat approach, with all participants analyzed in the group to which they were randomized, using a two-tailed 0.05 significance level. We will further conduct per-protocol analysis to evaluate the effect on levels of MVPA at 12 weeks among those who followed the study protocols. Both intention-to-treat and per protocol analyses will be performed on differences in the main and secondary outcomes between the two groups at 12-week and 12-month follow-ups. Mixed-effects regression models will be used for analyses accounting for baseline levels of MVPA and possible clustering of the randomized groups. Similar regression models will be fitted for secondary outcomes. Data will be presented as interclass correlation coefficients, adjusted mean differences (95% confidence interval) and corresponding *p* values. For the primary outcome, within- and between-group changes will also be calculated from a repeated-measures mixed-effects model.

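### The protocol gives two opposite orders for randomization and baseline testing, and neither as described puts the 7-day baseline accelerometer week before allocation unless devices go out earlier

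*Protocol article*

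**What the plan says.** The protocol article fixes the position of randomization twice.

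- Randomization: "Participants will be randomized before the first baseline assessment at the healthcare center".
- Baseline assessment: participants attend a group meeting, do physical tests and "fill in web-based questionnaires lasting, altogether, approximately 2 h". The section continues: "Thereafter, participants will be randomized into the two treatment groups, followed by separate introductions for their treatment".

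Three other sections bear on the timing of baseline MVPA.

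- Primary outcome: participants are to "wear the GT3X+ during all waking hours for seven consecutive days at baseline (week 0"), and again at weeks 6 and 12 and at 12 months. To be analyzed, a wear period needs "10 h of data on at least 4 days, including one weekend day".
- The eHealth program, Design: "The first consultation, held at the start of the intervention (baseline), will focus on information on how to use the apps".
- Primary and secondary outcome measures: the mixed-effects models are fitted "accounting for baseline levels of MVPA", and within- and between-group changes in MVPA are also to be reported from a repeated-measures model.

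The article does not say when the accelerometer is handed out or when the week-0 wear begins relative to allocation.

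**The concern.** There are two linked problems. The first is a plain contradiction about the order of the trial's key steps: site staff cannot both randomize before the baseline assessment and randomize after it.

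The second concerns the primary covariate. A baseline covariate can be adjusted for safely because randomization cannot have influenced it. A week of free-living activity recorded after participants have been allocated and introduced to their program does not have that property. Both programs ask participants to be more active from the outset, but in different ways. The eHealth arm gets a walking app and a home-training app for use three times a week. The supervised arm gets one supervised session and is encouraged to do two unsupervised sessions and to walk daily. If the arms respond differently in that first week, adjusting for it moves the estimated week-12 difference. A between-group comparison of change from baseline moves by more. A baseline week lost in this way cannot be collected again, and the Trial status section indicates that recruitment was under way.

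**Working it through.** **Step 1. The two orders side by side.** The protocol states no figure on this point, so the first check is of sequence.

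| Step | Order in Randomization | Order in Baseline assessment |
|---|---|---|
| 1 | Randomize | Tests and questionnaires, about 2 h |
| 2 | Baseline assessment | Randomize |
| 3 | Treatment introduction (position not restated) | Separate treatment introductions |

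Step 1 differs, so the two texts are incompatible.

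**Step 2. Can the wear week come before allocation?** The shortest usable wear is 4 days, and the planned wear is 7.

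- Under the Randomization order, every baseline measure, including the wear week, follows allocation.
- Under the Baseline assessment order, only about 2 h of testing at the meeting precede allocation. Neither 7 days nor 4 fit into 2 h, so wear comes first only if the device was issued before the meeting.
- No section describes earlier issue. Intervention design locates all measurements at the healthcare center, Study participants mentions no device at recruitment, and the eHealth Design section equates baseline with the start of the intervention.

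**Step 3. What follows if wear comes after allocation.** Inputs:

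- Target difference Δ = 10 min/day and SD = 25.1 min/day (Sample size calculation).
- Slope β of week-12 MVPA on baseline MVPA: not given. Assumed 0.3 to 0.7, equal to the correlation if the SDs are equal.
- Between-arm difference g already present in the week-0 recording because of allocation: not given. Assumed 1 to 5 min/day.

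Expected adjusted estimate = Δ − β × g. Expected between-group difference in change from baseline = Δ − g. If the true week-12 difference is 10 and g has the same sign:

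| | g = 1 | g = 3 | g = 5 |
|---|---|---|---|
| Adjusted, β = 0.3 | 9.7 | 9.1 | 8.5 |
| Adjusted, β = 0.5 | 9.5 | 8.5 | 7.5 |
| Adjusted, β = 0.7 | 9.3 | 7.9 | 6.5 |
| Change from baseline | 9 | 7 | 5 |

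The shift runs from 0.3 × 1 = 0.3 to 0.7 × 5 = 3.5 min/day. With g of the opposite sign, the adjusted estimate would be too large by the same amounts: 10 + 0.3 = 10.3 to 10 + 3.5 = 13.5. A simulation with 200,000 participants and SD 25.1 gave 8.59, 7.63 and 6.56 at g = 5, against 8.5, 7.5 and 6.5 from the formula. The simulation error is about 0.1.

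**Step 4. The neutral case.** If both arms rise equally in week 0, then g = 0 and the adjusted estimate stays at 10. Only the within-group changes are understated, by the amount of the common rise.

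**Step 5. A scale for g from the protocol.** A first-phase supervised session aims at a minimum of 10 min of MVPA once a week, or 10/7 = 1.4 min/day. A last-phase session gives 30/7 = 4.3 min/day. The upper assumed g of 5 is therefore generous for a first week. At g = 1.4 the shift is 0.3 × 1.4 = 0.4 to 0.7 × 1.4 = 1.0 min/day, and this still sets the eHealth arm's extra activity to zero.

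**The case against.** The strongest reply is that the wear dates are simply not stated. Participants are in contact with recruiting centers before the meeting, and consent precedes the baseline assessments. Devices could be issued in that interval, and an article commonly leaves such logistics to the full protocol or to a schedule figure that is not visible here. This stands in part. Wear after allocation is the natural reading of the sequence described, but it remains an inference. The reply does not touch the contradiction between the two sections, because the article states both orders.

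Several stronger readings are tempting, and the document does not support them.

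- A reader might infer that the covariate is already affected by treatment. The text supports only that it may be.
- A reader might infer that participants know their arm during fitness testing and questionnaires. The Randomization section does not say when allocation is disclosed, and the introductions are described as following the tests.
- A reader might infer that anyone found unsafe at baseline testing becomes a post-randomization exclusion. Participant safety gives that testing a safety purpose but states no exclusion rule, and the analysis is by intention to treat.
- A reader might infer that the bias always shrinks the effect. Both arms are active, so g could be near zero or of either sign.

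It is also fair to say that the size rests wholly on assumed values of slope and g.

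**Conclusion.** The point holds in limited form. The Randomization and Baseline assessment sections contradict each other, and that is explicit. As described, neither order lets the week-0 wear finish before allocation and the treatment introduction unless devices are issued beforehand, which no section describes. The baseline MVPA covariate and the change-from-baseline results are therefore exposed to an effect of allocation, but contamination is not shown.

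The shift of 0.3 to 3.5 min/day is 3% to 35% of the 10 min/day target (0.3/10 and 3.5/10). The top of that range combines the two most extreme assumptions, and a first-week g near the lower end is easier to reconcile with the gradual build-up of the programs. With no unequal early response there is no between-arm bias. The correction is warranted because it is cheap before allocation and impossible afterwards.

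**What to change.** 1. Delete the sentence in Randomization that places allocation before the baseline assessment, and keep the order in Baseline assessment: test, then randomize, then introduce treatment.
2. Issue or post the GT3X+ after consent, so that the 7-day wear is complete before randomization.
3. In Primary outcome, state the start and end of the week-0 wear relative to allocation.

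The cost is device hand-out about one week earlier, possibly by mail, with consent taken before that point. Study participants already places consent ahead of the baseline assessments, but if it is in practice taken at the meeting, it would need an earlier contact. If devices already go out before the meeting, one sentence saying so and the correction to Randomization are enough.

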### Baseline assessment

Participants will be invited to group consultation meetings, including baseline assessments, at a healthcare center. The group consultations will be held at three time points and include all participants recruited from the different recruitment sources.

After a short introduction, participants will perform a battery of physical tests and fill in web-based questionnaires lasting, altogether, approximately 2 h. Thereafter, participants will be randomized into the two treatment groups, followed by separate introductions for their treatment. In addition to the questionnaires described below, the participants will fill in questions on basic demographic information. The baseline measures and all follow-up measures will be made in the morning (fasted state) in order to best utilize standardize measures (e.g. blood samples).

### Primary outcome

The primary outcome, difference in time spent in MVPA per day at 12 weeks between the two groups, will be measured using the Actigraph GT3X+ tri-axial accelerometer (Actigraph, LCC, Pensacola, FL, USA), which has shown to accurately assess levels of PA under free-living conditions [27, 28]. Participants will be asked to wear the GT3X+ during all waking hours for seven consecutive days at baseline (week 0), midpoint (week 6), endpoint (week 12) and at maintenance follow-up (12 months). The minimum data requirement for inclusion in the analyses will be 10 h of data on at least 4 days, including one weekend day. Management and analyses of PA data will follow best practice and research recommendations [29]. In addition, we will analyze time spent in light and vigorous PA and sedentary time at all measure time points, as well as day-to-day data on steps/day from the participants’ smartphones (automatically stored in each smartphone “health kit” application).

### Secondary outcomes

Measures on secondary outcomes, aside from the semi-structured interviews on intervention adherence and enjoyment, will be taken at baseline (week 0), midpoint (week 6), endpoint (week 12) and at maintenance follow-up (12 months).

### Body composition measures

The physical tests include measures on body composition: height, weight, waist circumference, fat mass and fat-free mass via bioelectrical impedance [30]. Body mass and height will be measured with the participants wearing light clothes to the nearest 0.1 kg and 0.5 cm, respectively. An Omron model HBF-511B-E/HBF-511 T-E will be used for the bioelectrical impedance measures.

### Fitness tests

Fitness will be measured via a submaximal VO_2_max test performed on a stationary bike to assess aerobic fitness [31]. The participants will be instructed to cycle, with a pedal frequency of 60 rpm and a resistance of 0.5 kilopond (29 W), on a calibrated, mechanically braked, cycle ergometer (model 828E, Monark, Varberg, Sweden) during 4 min. Thereafter, the loading is progressively increased until the subject reaches a heart rate of 120 beats per minute. The mean pulse during the last minute is recorded. VO_2_max is the estimated by sex- and age-specific equations on differences in pulse rate between the higher and lower standard load.

### Blood sample measures

In addition, blood samples will be collected at weeks 0, and 12, as well as at 12 months. All blood samples will be procured by means of an intravenous cannula. At each sampling, the first 2 mL of the draw will be discarded as waste before a 5-mL sample is collected. This sample will then be dispensed in to an EDTA tube, a plasma-heparin tube and a serum tube. The two latter samples will be centrifuged at 1700 g for 20 min before initial storage in − 20 °C and later storage at − 80 °C pending subsequent analysis for genetic/epigenetic and metabolomics analysis. All blood samples will be sent to and stored at a Biobank at Karolinska Institutet.

Analyse of blood will include markers of inflammation and stress. Genetic single-nucleotide polymorphism and epigenetic methylation status genome-wide analysis will be performed using the Illumina-based platform [32] from blood samples taken at weeks 0, and 12. The genetic/epigenetic analyses will enable the current study to investigate the extent to which the intervention effects are driven by genetic/epigenetic factors, which, in twin studies, have shown to play a major role in responsiveness to PA within an intervention setting [33].

### Web-based questionnaire measures

Participants will answer a web-based survey measuring the following aspects:HRQoL by the SF-36 [34], a widely-used instrument which measures HRQoL with 36 questions divided in eight dimensions: physical functioning, role limitations due to physical health problems, bodily pain, general health, vitality, social functioning, role limitations due to emotional problems and mental healthMusculoskeletal pain on a Visual Analogue Scale from zero (no pain) to 100 (worst imaginable pain) over the past week [35, 36]Perceived stress by the Perceived Stress Scale [37], a 10-item questionnaire (scored 0–4) based on how the respondent felt during the past monthSymptoms of depression by the Beck Depression Inventory-II [38], one of the most widely used psychometric scales for measuring the severity of depression by a 21-item, multi-choice, self-report inventoryWork ability via the Work Ability Index (WAI) scale [39], a questionnaire designed to quantify an individual’s capacity for work, comprising seven dimensions and including such questions as, “Assuming that your work ability at its best has a value of 10 points how many points would you give your current work ability?”Dietary intake by 24 h recall [40], a structured interview (administered by a trained interviewer) intended to capture detailed information about all foods and beverages consumed by the respondent in the past 24 h, from midnight to midnight the previous dayMotivation towards PA and exercise will be measured by the Behavioral Regulation in Exercise Questionnaire [41], a 19-item questionnaire measuring the stages of the self-determination continuum with respect to motivation to exercise by a 5-point Likert scale (ranging from not true for me to very true for me)

### Qualitative interview measures

At the endpoint (week 12) and after 12 months, a purposive sample of participants from each arm will participate in individual semi-structured interviews or focus group discussions to qualitatively assess the efficacy, implementation and outcomes of the programs and their experiences of persistent lifestyle changes. All interviews are performed by trained health educators and digitally recorded. The interviews are transcribed to text verbatim and thereafter analyzed.

### Participant safety

Participant safety will be a main priority, and multiple strategies will be utilized to minimize adverse events associated with participation in the study. The supervised baseline testing session will ensure that participants are safe to participate in the planned intervention and assessments. Adverse events will be tracked closely, during meetings and research assessments, with special emphasis on events that could be associated with participation in the study.

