### The eHealth program

#### Short description

The eHealth program is a 12-week, standardized walking, exercise and food photography program, delivered via smartphone apps, with three face-to-face meetings with health educators (*n* = 55).

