### Design

The intervention framework is based on a recent systematic review concluding that multi-component application-based interventions to improve diet, PA and sedentary behaviors can be effective [13], especially if the intervention entails app-embedded behavior-change techniques [18]. In addition, individually tailored feedback, based on the participant’s own characteristics, and advice is more likely to be effective compared with generic information about health benefits from PA [16, 19]. The Acupedo walking app will be used in the current study. The app is the number-one-ranked pedometer app at the app/google app store and comprises several behavior-change techniques, which is important when promoting PA [18]. In addition, participants will be encouraged to use an individually tailored home-based training app (three times/week) developed by the Swedish Military. This app comprises a pre-defined 12-weeks exercise program with progressively increasing exercise intensity. Both apps contain several behavior-change techniques: for example, self-monitoring and specific goal setting. Furthermore, participants will use food photography, via an app, a methodology shown to assess food intake in different environments with acceptable accuracy [20, 21]. Additionally, food photography holds promise as an intervention tool to change dietary decision-making and attitudes [22].

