The intervention will encompass both structured supervised and non-supervised PA including aerobic, strength, flexibility and balance training, and will be designed to be performed at fitness centers with personal trainers, one time per week with a total of 12 sessions during the intervention period. PA goals will be individualized based on each participant’s level of physical fitness (VO_2_max), and will further be modified in response to illness, injury or physical symptoms. Participants will be further encouraged to have an active lifestyle with two more weekly un-supervised exercise sessions. Participants will further be encouraged to avoid prolonged periods of uninterrupted sitting and aim at a minimum of 30 min daily walking. The weekly personal trainer supervised exercise sessions, lasting 60 min each, will target compound movements, involving large muscle groups. The exercise sessions during the first 4 weeks will aim at for a minimum of 10 min of PA at a moderate to vigorous intensity (> 60% VO_2_max). During the next 4 weeks, time in MVPA will progressively increase to 20 min per session and the last 4 weeks of the intervention will provide 30 min of MVPA per exercise session. Exercise sessions will be 60 min long throughout the intervention period. Thus, lower-intensity PA, such as balance and flexibility training, will be progressively replaced during the intervention period. The exercise sessions will be structured so that they can be generalized to the home environment; thus, possibly increasing post-intervention maintenance. Interviews with a purposive sample of participants will be performed at 12 weeks focusing on experiences of the efficacy, implementation and outcomes of the program and again at 12 months to explore persistent changes in lifestyle.

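### Adverse-event capture is tied to contacts that are weekly in one arm and six-weekly in the other, so any side-by-side count would tend to favour eHealth

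*Protocol article*

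**What the plan says.** All references are to the protocol article.

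- **Capture rule (Participant safety).** "Adverse events will be tracked closely, during meetings and research assessments", "with special emphasis on events that could be associated with participation in the study". No other route is named.
- **eHealth contacts (The eHealth program, Short description and Design).** The programme comes "with three face-to-face meetings with health educators". The Design section adds: "The intervention entails three face-to-face consultations, in groups of approximately 20 participants". The first is at baseline; the others are "The second PA consultation, held at week 6" and "The final meeting at week 12".
- **Supervised contacts (The supervised health program, Design).** Trainer-led exercise takes place "one time per week with a total of 12 sessions during the intervention period". The same section uses the word *meetings* for contacts with health educators and personal trainers. It also says that activity goals are adjusted for illness, injury or symptoms.
- **Research assessments (Primary outcome; Secondary outcomes).** Weeks 0, 6 and 12 and 12 months, in both arms.
- **Unsupervised training.** Encouraged three times a week in eHealth through an app ("This app comprises a pre-defined 12-weeks exercise program with progressively increasing exercise intensity") and twice a week in the supervised arm.
- **Analysis (Statistical analyses).** Between-group analyses are planned for the main and secondary outcomes. Adverse events are not among them.

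**The concern.** When events are recorded at contacts, the arm with more contacts has more chances to have an event recorded. Here the contact schedule is part of the treatment, so the number of chances differs by design. A trainer who sees a participant every week, and who adjusts goals for injury and symptoms, is likely to hear of a minor strain within days. An eHealth participant with the same strain may not meet staff for up to six weeks, and by then may have forgotten it or not think it worth mentioning.

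In a two-arm trial, adverse-event counts by arm tend to be read side by side even when no test is planned. The Significance section foresees wide use of the app programme if it proves effective. A lower count in eHealth could then be taken as reassurance when it partly reflects less observation. Events not recorded at the time cannot be recovered at analysis.

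**Working it through.** The article gives no adverse-event figure to reproduce, so the check counts capture opportunities and then tests how much they could matter.

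**1. Capture weeks after baseline, weeks 1 to 12**

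- eHealth: meetings at weeks 6 and 12 and assessments at weeks 6 and 12. These coincide, giving 2 capture weeks. The baseline meeting cannot capture an on-programme event.
- Supervised: 12 weekly sessions. The assessments at weeks 6 and 12 fall in weeks that already have a session, giving 12 capture weeks.
- After week 12 the only stated capture point is 12 months, in both arms.

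**2. Wait from event to next contact**

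Assume that events are spread evenly over the 12 weeks, that contacts fall at the end of each interval and that attendance is full. With contacts every L weeks, the mean wait is L/2 and the longest is L.

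- eHealth, L = 6: mean 6/2 = 3.0 weeks, longest 6.
- Supervised, L = 1: mean 1/2 = 0.5 weeks, longest 1.

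**3. What that could do to counts (assumed recall)**

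Suppose that the chance of an event being reported halves every h weeks until the next contact. The expected share captured is

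(1 − 2^(−L/h)) / (ln 2 × L/h).

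For h = 2:

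- eHealth: (1 − 2^(−3)) / (0.693 × 3) = 0.875 / 2.079 = 0.42.
- Supervised: (1 − 2^(−0.5)) / (0.693 × 0.5) = 0.293 / 0.347 = 0.85.

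| Assumed half-life h | eHealth captured | Supervised captured | Apparent ratio, supervised : eHealth |
|---|---|---|---|
| 2 weeks | 42% | 85% | 2.0 |
| 4 weeks | 62% | 92% | 1.5 |
| 8 weeks | 78% | 96% | 1.2 |
| 26 weeks | 92% | 99% | 1.07 |

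The true event rates are equal in every row. The half-lives are not from the article. A serious event would behave like the bottom row or better; a minor ache might behave like the top one. With no loss of recall the ratio is 1.

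**4. Shared capture points only**

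If only the assessments at weeks 6 and 12 are used, both arms have 2 capture points and a mean wait of 3.0 weeks, so the schedule no longer produces a difference.

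**The case against.** The strongest reply is that the article plans no between-arm comparison of adverse events. They are neither a primary nor a secondary outcome, and the safety section describes monitoring of participants, where more frequent contact is no fault. This stands. A reader might infer that a planned comparison is biased; the document does not support that, because it contains no such comparison. The point concerns how counts by arm could be read.

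Second, the research assessments are common to both arms and already offer a like-for-like base. This also stands, and the fix builds on it. But the stated rule names meetings and assessments together and does not say that the two sources are kept apart.

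Third, the safety section does not itself say that trainer sessions are meetings. True: that rests on how the supervised programme's Design section uses the word. It is a fair reading, not a certainty.

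Fourth, an article condenses its protocol, and forms, definitions and recorders may be set out elsewhere. Their absence is not criticised here. The point rests only on the capture rule and schedules that the article does state.

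Some further inferences should be resisted:

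- That events in home training are missed in eHealth in particular. Both arms train unsupervised, and an event can still be reported at a later contact. The week-6 eHealth meeting includes interviews about barriers to adherence, where an injury could well come up.
- That the trainer sessions are one-to-one, or that programme staff judge whether an event is related. The article says neither.
- That the roll-out argument rests on a safety advantage. The Significance section argues from cost, reach and effectiveness.

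**Conclusion.** The point holds in a limited form. Following the stated rule, and reading trainer sessions as meetings, ascertainment during the 12 weeks is unequal by design: 2 capture weeks against 12, with a mean wait of 3.0 against 0.5 weeks. Delayed or missed capture is a risk in both arms, but weekly contact reduces it in only one. If recall fades at all, equal true rates would show as fewer recorded events in eHealth.

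The size cannot be determined from the article. The ratio of about 1.07 to 2.0 depends wholly on the assumed recall half-lives of 26 to 2 weeks, and on evenly spread events and full attendance. The planned efficacy analyses are unaffected. This is an inexpensive improvement to safety reporting, not a flaw in the trial's main comparison.

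**What to change.** 1. Add one short adverse-event and injury checklist to the existing web survey at weeks 6 and 12 and at 12 months, identical in both arms, asking about any event since the previous survey, whatever the cause.
2. State that any between-arm safety summary uses those records only.
3. List events noted only at trainer sessions separately by arm, so that nothing learned through closer contact is lost and nothing from it enters the comparison.

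Asking about any cause also keeps the comparison free of a judgement on relatedness; the intended emphasis on participation-related events can remain as a descriptive listing.

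The cost is a few items in a questionnaire that participants already complete at these visits, with no change to visits or interventions. The price is some recall error: a mean wait of 3.0 weeks during the programme, and longer before the 12-month survey. The recall window is the same in both arms.
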